### Interim analysis

An interim analysis will be conducted by statisticians when 20 subjects complete the experiment. In our study, the primary endpoint will be analyzed via the change of Cobb angle. In order to maintain the cumulative type I error rate at the planned 0.05, the Lan-Demets spending function method [62] with the O’Brien-Fleming spending function [63] will be used. The preplanned *P* value for stopping the trial owing to efficacy will be 0.00305. Our research team will discuss the results of the interim analysis with the ISC and the monitoring board to determine whether to stop the trial early. Besides, when a serious adverse event occurs in our study, the trial will also be terminated early.

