### Assessment

Age, sex, height, weight, Risser sign, menarche status (for the girls), and type of scoliosis will be recorded at the start of the experiment. The United States Risser staging will be used to quantify skeletal maturity on a scale of 0 to 5 [43]. Stage 0 represents no ossification of the iliac apophysis, whereas stage 5 represents complete ossification and fusion. The scoliosis types will include thoracic, lumbar, thoracolumbar, and S-shaped scoliosis, corresponding to the anatomical site of the spinal deformity [1].

The primary outcome will be the feasibility of performing a full-scale study using these protocols. The time to complete enrollment, recruitment rate, subject retention, and adherence to the treatment allocation will all be important observations. The efficacy of treatment will be the secondary outcome. Spine curvature, rotation of the trunk, and postural symmetry will be assessed by the Cobb angle from X-ray images; the ATR, as measured with a Scoliometer; and 3-DPPs, as measured using a global postural system (GPS), respectively. The SEP will be assessed for evaluating sensorimotor integration, and the SRS-22 will be administered for the quality of life. The Cobb angle will be measured at baseline and at the end of 8 weeks of training. The SEP will be measured at baseline and at the end of 2 weeks of training. The ATR, 3-DPPs, and SRS-22 scores will be measured at baseline and then after 2 weeks, 4 weeks, and 8 weeks of treatment. The mean changes of Cobb angle from baseline to the end will be compared. And the mean difference of other indicators between each two visits will be used for comparative analysis.

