### Primary outcomes

The primary outcome of the study will be a judgment about the feasibility of conducting a full-scale RCT. The specific aspects of feasibility that will be monitored are listed below.

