### Sample size

G*Power 3.1.9.7 was used to execute the power calculations. The change of the Cobb angle was chosen as the primary outcome indicator. Referring to the two studies from Zheng (*d* = 0.8) [59] and Liang et al. (*d* = 1.2) [60], we set the value of effect size *d* = 1.0 in our study. With a significance level of 5%, 17 subjects are needed in each group to reach a power of 80%. Allowing for a dropout rate of 15%, a total of 40 subjects will be recruited with 20 subjects for each.

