### Data collection, data management, and statistical analysis

The primary outcome measures will be tabulated and interpreted with respect to the goals established a priori.

To estimate the sample size required for a future full-scale RCT, between-group effect sizes and their 95% confidence intervals will be calculated by applying Hedges’ correction. A minimum power of 80% will be used to detect changes in the Cobb angles, ATRs, 3-DPPs and SRS-22 scores (*α* = 0.05). The sample size will be increased to allow for an estimated 20% dropout rate. Statistical methods for the secondary outcome measures will be evaluated via comparisons of changes between groups.

The data will be double entered into EpiData 3.1 software (The EpiData Association, Odense, Denmark) and then transferred to version 22.0 of the SPSS software suite (IBM, Armonk, NY, USA) for the analyses. The threshold for significance will be taken as *α* ≤ 0.05. A statistician who will be blinded to the allocation results will analyze all the data. The continuous variables will be presented as means ± SDs, and the categorical variables will be presented as ratios. The baseline readings will be compared using independent samples *t* tests or chi-squared tests. For the Cobb angles and SRS-22 scores, independent samples *t* tests will be used to compare the two groups, and paired *t* tests will be used for within-group comparisons. For the M, U, MU, and M+U SEP peak amplitudes and latencies, nonparametric Wilcoxon signed-ranks tests will be used to compare these values between and within the groups. For the 3-DPPs and ATR, repeated measured analysis of variance will be used for the between-groups and within-groups comparison. Furthermore, we will perform subgroup analysis by age group (age < 13 years and age ≥ 13 years) [2, 33]. To deal with the missing data, a sensitivity analysis and weighted estimating equations will be used as the primary approach [61].

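### A pilot with a feasibility primary outcome calls Cobb angle change primary elsewhere and allows an efficacy stop on it at 20 completers; a stop would cut the feasibility data and pass on a selected effect size

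*Protocol article*

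**What the plan says.** All references are to the protocol article.

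- **Feasibility is primary.** Primary outcomes: "The primary outcome of the study will be a judgment about the feasibility of conducting a full-scale RCT". The Abstract agrees and names time to complete enrolment, recruitment rate, retention and adherence. Assessment adds: "The efficacy of treatment will be the secondary outcome". The Cobb angle is listed under Secondary outcomes.
- **Cobb angle is primary.** Sample size: "The change of the Cobb angle was chosen as the primary outcome indicator". Interim analysis: "In our study, the primary endpoint will be analyzed via the change of Cobb angle".
- **The look.** Interim analysis: "An interim analysis will be conducted by statisticians when 20 subjects complete the experiment". Lan-DeMets spending of O'Brien-Fleming type is to hold cumulative type I error at 0.05, and the P "value for stopping the trial owing to efficacy will be 0.00305". The research team discusses the result with the Independent Supervisory Committee and the monitoring board before any decision.
- **Later use of the effect sizes.** Under Primary outcomes, the pilot's largest between-group effect selects the full trial's primary outcome measure, and the pilot's effect sizes determine its sample size.
- **Significance level.** The statistical analysis section has a general statement, "The threshold for significance will be taken as" α ≤ 0.05. No separate level is printed for the final Cobb test after the interim look.

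**The concern.** The two labels for the primary outcome matter because a rule that can end the trial hangs on one of them. The rule acts on a measure that the outcome sections call secondary, and no feasibility criterion is attached to the look.

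Both stated aims of the pilot would suffer from a stop. The feasibility quantities are observed by running recruitment and treatment to the end. The effect size is wanted as an input to the full trial, and an efficacy boundary at 20 subjects lets the trial end early only when the observed difference is extreme. An estimate obtained that way is selected to be large and would lead to a full trial that is too small.

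**Working it through.** **Inputs.** Interim at 20 completers, 40 planned, 1:1 allocation, cumulative error 0.05, interim P 0.00305, d = 1.0, 17 per group for 80% power, 15% dropout. Assumptions: two-sided testing (sidedness is not stated) and 10 per arm at the look (simple randomization may give unequal arms).

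**1. The protocol's own figures.** With 0.025 per tail, the error spent at information fraction t is 2 × [1 − Φ(z(0.9875)/√t)]. At t = 20/40 = 0.5 this is 2 × [1 − Φ(2.2414/0.7071)] = 0.001525 per tail, or 0.00305 two-sided. The printed level reproduces. So does the sample size: the noncentral t gives power 0.807 with 17 per group at d = 1.0, and 17/0.85 = 20 per group.

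**2. What a stop requires.** P < 0.00305 on 18 df needs |t| > 3.42. The observed d must then be at least 3.42 × √(2/10) = 1.53. With the Hedges factor 1 − 3/(4 × 18 − 1) = 0.958, g must be at least 1.47.

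**3. How often, and what estimate results** (noncentral t for the probability; simulation with 500,000 replicates per effect for the mean):

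| True d | Chance of crossing | Mean g given a crossing |
|---|---|---|
| 0.5 | 2.4% | 1.70 |
| 0.8 | 8.3% | 1.75 |
| 1.0 | 16% | 1.78 |

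Hedges' correction deals with small-sample bias. It does not remove selection by the boundary.

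**4. Consequence for the full trial.** Planning on g of about 1.75 at 80% power gives 7 per arm. With 7 per arm, power is 0.41 if the true d is 1.0 (17 per arm needed) and 0.14 if it is 0.5 (64 per arm needed).

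**5. Consequence for feasibility.** Twenty completers at 15% dropout imply 20/0.85 ≈ 24 enrolled. If 40 subjects accrue evenly over the 24-month recruitment window (Trial status), 40/24 × 8/4.33 ≈ 3 more enter during one 8-week course, about 27 in all. Exact 95% intervals near the 80% adherence goal:

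| Subjects meeting the goal | Observed | 95% CI |
|---|---|---|
| 32 of 40 | 80% | 64% to 91% |
| 22 of 27 | 81% | 62% to 94% |
| 16 of 20 | 80% | 56% to 94% |

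Time to complete enrolment of 40 would not be observed at all.

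**6. Overall error.** From the bivariate normal with correlation √t, the final level that matches 0.00305 at t = 0.5 is 0.0490 (z = 1.969). Testing at 0.05 instead gives 0.0510 overall.

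**The case against.** **The harm is conditional.** It needs a crossing, with 2.4% to 16% probability over the effects considered, and then a decision by the team after discussion with two bodies. Averaged over stopped and continued trials, mean g is only about 1.06 to 1.07 at true d = 1.0 and 0.51 to 0.52 at d = 0.5. This stands, and it limits how often the damage occurs. It does not give the rule a purpose in a feasibility pilot.

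**The feasibility loss can be overstated.** Recruitment rate and adherence would already be observed on more than half the sample, and the planned interviews could still be held. This also stands: 16 of 20 is the worst case, and about 27 enrolled is more realistic. Time to complete enrolment is the part wholly lost.

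**The imprecision would be visible.** The protocol reports a 95% interval with each effect size; at the boundary it runs from about 0.51 to 2.52 for d. The full trial's sample size is also to consider ATR, posture and SRS-22, so 7 per arm assumes planning on the Cobb point estimate alone. Both are fair, but an interval does not correct a selected point estimate, and choosing the outcome with the largest effect would favour Cobb after a stop.

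**Two stronger readings on alpha are tempting.** A reader might infer that the final test is not adjusted for the look. The Interim analysis section names a spending function to hold 0.05, so adjustment is intended; the matching level is merely unprinted and not reconciled with the general 0.05. A reader might also infer that error control is incomplete because 34 evaluable subjects are expected, making the fraction 20/34. At that fraction the boundary would be 0.0069, so 0.00305 is stricter than needed, and 0.00305 followed by 0.0490 gives 0.0497 overall. Neither reading is supported.

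**Conclusion.** The concern holds as a contradiction over which outcome is primary, combined with a stopping rule that does not fit the trial's purpose. As written, an efficacy stop would leave one named feasibility quantity unobserved, reduce retention and adherence data to roughly 20 to 27 subjects, and hand the full trial an effect of at least g = 1.47, on average 1.7 to 1.8, where 1.0 was assumed. The boundary itself is computed correctly. The missing final level is a minor matter, an excess of 0.001.

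The figures assume two-sided testing, normal outcomes and 10 per arm at the look. The figure of 27 further assumes 15% dropout and even accrual over 24 months.

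**What to change.** 1. In Sample size and Interim analysis, call Cobb angle change the main secondary (efficacy) outcome, so that feasibility is the single primary outcome. The calculation of 17 per group can stay under that label.
2. Replace the efficacy stop with a safety and feasibility review at 20 completers that has no between-group efficacy test.
3. If the sponsor keeps the efficacy look, state 0.0490 as the final level for the Cobb test at half information in place of the general 0.05, and commit to a bias-adjusted effect size after any early stop.

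The cost is wording in two sections, or three under the third option, with no added subjects or visits. The sponsor gives up an efficacy stop with about a 16% chance of being crossed under its own assumption.

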**Methods:**

The protocol describes a randomized controlled pilot trial with 40 subjects divided into study and control groups. Both groups will receive 8 weeks of PSSE, but the study group will also receive spinal manipulative therapy during the first 2 weeks before PSSE. The primary outcome will be an estimate of the feasibility of conducting a full-scale experiment. The influencing factors will be the time to complete enrollment, the recruitment rate, subject retention, and adherence to the treatment allocations. The secondary outcomes that will be used to assess the efficacy of treatment will include the Cobb angle, somatosensory evoked potentials, ATR, three-dimensional postural parameters, and scores on the 22-item Scoliosis Research Society outcomes questionnaire. The Cobb angle will be measured at baseline and at the end of 8 weeks of training. The somatosensory evoked potentials will be measured at baseline and at the end of 2 weeks of training. The ATR, three-dimensional postural parameters, and scores on the 22-item Scoliosis Research Society outcomes questionnaire will be measured at baseline and at 2 weeks, 4 weeks, and 8 weeks of treatment.

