#### Recruitment and retention

The goal is to enroll at least 80% of the eligible subjects recruited. Once the subjects are enrolled, the goal will be that at least 80% of the subjects attend at least 75% of the treatment sessions and complete at least 75% of the prescribed exercises.

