#### Sample size calculation

The sample size needed for a full RCT will be estimated using the effect-size data from this pilot study.

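### The interim rule allows an efficacy stop on the Cobb angle, a secondary outcome, in a pilot whose primary outcome is feasibility and whose effect size feeds the full trial

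*Protocol article*

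**What the plan says.** The protocol article ranks its outcomes clearly in some sections and reverses the ranking in others.

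- **Feasibility is primary.** Primary outcomes states: "The primary outcome of the study will be a judgment about the feasibility of conducting a full-scale RCT". The Abstract (Methods) lists the components: "The influencing factors will be the time to complete enrollment, the recruitment rate, subject retention, and adherence to the treatment allocations". Assessment repeats the list and adds: "The efficacy of treatment will be the secondary outcome".
- **Feasibility goals.** Recruitment and retention sets proportions, among them that "at least 80% of the subjects attend at least 75% of the treatment sessions and complete at least 75% of the prescribed exercises". It sets no numerical goal for time to complete enrollment.
- **The Cobb angle is called primary elsewhere.** Sample size takes the change of Cobb angle as the primary outcome indicator (d = 1.0, 17 per group for 80% power, 40 recruited with 15% dropout). Interim analysis calls it the primary endpoint.
- **The interim rule.** "An interim analysis will be conducted by statisticians when 20 subjects complete the experiment". Lan-DeMets spending of O'Brien-Fleming type is used, and the preplanned P "value for stopping the trial owing to efficacy will be 0.00305". The research team then discusses the result with the Independent Supervisory Committee (ISC) and the monitoring board before deciding whether to stop. No feasibility criterion enters the efficacy rule.
- **Use of the effect size.** Under Sample size calculation: "The sample size needed for a full RCT will be estimated using the effect-size data from this pilot study". Primary outcome measure selects the full trial's primary outcome by the largest between-group effect size. The statistical analysis section specifies Hedges' correction with 95% confidence intervals and states no adjustment for early stopping.

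**The concern.** An efficacy boundary suits a trial whose purpose is to answer an efficacy question. This pilot is meant to deliver a feasibility judgment and planning estimates for a larger trial. A stop on the Cobb angle at the halfway point helps with neither. One feasibility measure, time to complete enrollment, can only be observed if enrollment is completed, and the others would rest on fewer subjects. A trial that stops has also been selected for a very large observed effect, and that effect is then used to choose the outcome and set the size of the full trial. The contradiction over which outcome is primary lies beneath this: the interim rule is coherent only if the Cobb angle is primary, which the outcome sections deny.

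**Working it through.** **Inputs from the article.** 40 subjects allocated 1:1; interim at 20 completers; overall alpha 0.05; interim P = 0.00305; planning d = 1.0; 15% dropout; independent samples t test for the Cobb angle; recruitment from 1 November 2019 to 1 November 2021 (24 months); 8 weeks of treatment. Sidedness is not stated; two-sided testing reproduces the stated figures. The true d is unknown, so a range is shown.

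**1. The plan's own figures.** O'Brien-Fleming-type spending at information fraction 20/40 = 0.5, with 0.025 in each tail:

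4 × [1 − Φ(z₀.₉₈₇₅ / √0.5)] = 0.00305, as stated.

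The two-sided noncentral t at d = 1.0 gives power 0.807 with 17 per group (0.781 with 16), and 17 / 0.85 = 20 per group. Both figures reproduce.

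**2. Smallest effect that crosses the boundary, 10 per arm.**

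- Critical |t| on 18 df at P = 0.00305: 3.42
- d = 3.42 × √(2/10) = 1.53
- Hedges factor: 1 − 3/(4 × 18 − 1) = 0.958
- g = 1.53 × 0.958 = 1.47

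Simple randomization can give unequal arms; a 7:13 split raises the minimum g to 1.54.

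**3. Chance of a favourable stop, and the estimate reported if it happens** (simulated two-sample t tests, 10 per arm).

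| True d | Chance of stop | Mean g given stop |
|---|---|---|
| 0.5 | 2.4% | 1.70 |
| 0.8 | 8.4% | 1.74 |
| 1.0 | 16.1% | 1.78 |
| 1.2 | 27.5% | 1.82 |

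**4. The whole procedure** (interim at 10 per arm, otherwise continuing to 17 per arm; 400,000 simulated trials per scenario). Mean g over all trials, stopped or not:

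- true d = 0.5: 0.51 (about 3% high)
- true d = 0.8: 0.84 (about 5% high)
- true d = 1.0: 1.06 (about 6% high)

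At d = 1.0, the same trials that would have stopped average g = 1.43 if continued to 17 per arm. Continuing therefore removes (1.78 − 1.43) / (1.78 − 1.00) = 0.35 / 0.78, or about 45%, of the excess in those trials. The rest is a favourable first half that the final data still contain.

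**5. Feasibility data at a stop.** Assume even accrual of 40 over 24 months, or 1.67 per month. Eight weeks is about 1.84 months, so about 1.67 × 1.84 = 3.1 subjects would still be in treatment.

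- No dropout: 20 + 3.1 ≈ 23 enrolled
- 15% dropout: 20/0.85 + 3.1 = 26.6, about 27 enrolled

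Time to enroll 40 is then not observed. The loss of precision on the proportions is modest: for an observed 80%, the Wilson 95% interval is 58–92% with n = 20 and 65–90% with n = 40.

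**6. Final-look alpha.** With 0.00305 spent at the interim, the final two-sided level that holds 0.05 overall is about 0.0490. Without the interim test it is 0.05.

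**The case against.** The strongest reply has four parts.

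**The stop is advisory.** The ISC and the monitoring board discuss the result first and could weigh the lost feasibility data. This stands. It makes a stop less likely, but it does not supply a feasibility criterion.

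**Most of the primary outcome would survive.** A reader might infer that a stop ends the pilot before its primary outcome is observed. The article does not support that. Protocol integrity, the blinding interviews, recruitment rate, retention and adherence can all be assessed at the interim, and the numerical goals are proportions that do not require 40 subjects. Only time to complete enrollment is lost outright.

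**The inflation is conditional.** A reader might also infer that the rule hands the full trial a grossly inflated effect. That holds only in trials that stop, which are a minority at every d examined. The average bias is small, and continuing removes only part of the excess in the trials concerned. Nor does it follow that the full trial would be sized on the Cobb point estimate alone: the statistical analysis section asks for 80% power on the Cobb angle, ATR, postural parameters and SRS-22, with confidence intervals. With 10 per arm, g = 1.78 has an approximate interval of 0.74 to 2.82, so its imprecision would be visible.

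**An efficacy look is coherent if the Cobb angle is primary**, as Sample size and Interim analysis say. This is true, but it restates the contradiction. Primary outcomes and Assessment say otherwise, and the passages cannot all stand.

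**Conclusion.** The concern holds in a limited form. The efficacy stop is tied to an outcome that the article ranks as secondary, and other sections of the article contradict that ranking. The number 0.00305 is not in error.

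If the rule operates, time to complete enrollment is lost and the remaining feasibility measures rest on about 23 to 27 enrolled subjects instead of 40. The reported g is at least 1.47 and averages 1.70 to 1.82 for true d from 0.5 to 1.2, with no stated adjustment before it is used for planning. The chance of this is 16% at the plan's own d = 1.0 and below 10% at d of 0.8 or less. Over all trials the bias is about 3 to 6% for true d from 0.5 to 1.0.

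These figures assume two-sided testing, equal arms of 10 at the interim and 17 at the end, normally distributed outcomes, a stop whenever the boundary is crossed, and even accrual for the enrollment count. Since the bodies consulted may decide not to stop, the stopping chances are upper figures for each d under these assumptions.

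**What to change.** Provided the interim look has not yet been taken, which the article does not show:

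1. In Interim analysis, delete the efficacy boundary and the comparative Cobb test. Make the review at 20 completers one of safety, recruitment, retention and adherence.
2. State that, for efficacy purposes, enrollment continues to 40. This leaves the article's separate provision on serious adverse events untouched.
3. In Sample size and Interim analysis, reword so that the Cobb angle is the secondary outcome used for the sample size calculation, in line with Primary outcomes and Assessment.

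The cost is a protocol amendment during recruitment and the loss of the option to stop early for efficacy, a 16% chance at d = 1.0. In return, time to complete enrollment can be observed and the planning estimate is no longer selected on crossing a boundary. The final Cobb test also keeps the full 0.05 instead of about 0.049, a negligible gain that is not itself a reason for the change. If the look has already been taken, that should be disclosed, and the full 0.05 can no longer be claimed.
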